### Statistical analysis

Statistical analysis will be performed using SAS 9.3 software by an independent statistician. All statistical tests will use a two-sided test, *P* ≤ 0.05 will be regarded as significant. A 95% confidence interval will be used. Based on the intention-to-treat principle, the missing data will be replaced by the last data (i.e., the missing efficacy data will be replaced by the efficacy data of the previous follow-up). The efficacy analysis will be mainly based on a full analysis set, and the central effect will be considered. The primary efficacy endpoint will be tested for superiority. The efficacy between groups will be compared using the Cochran-Mantel-Haenszel-*χ*^2^ test with and without regard to center stratification, and a 95% confidence interval of the difference between groups will be calculated. Method repetitive measure analysis of variance will be used to analyze the secondary outcome of VAS scores at different time points between groups. Sub-analysis will be carried out to review whether there is a difference in the effect of ZZKZ according to demographical data across countries. The safety analysis will be mainly based on descriptive statistics. The adverse events that occur in this trial will be described in a list, and the incidences will be compared using Fisher’s exact probability test.

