#### Secondary outcomes

##### VAS score of each FD symptom

On the diary cards, subjects will be recorded the VAS of each FD symptom daily, including abdominal distension (mid-epigastric distension or lower abdominal distension), abdominal pain (mid-epigastric pain or lower abdominal pain), epigastric burning sensation, nausea, excessive eructation, heartburn, vomiting, regurgitation, dysphagia, abdominal enlargement, and defecation smoothness [20]. VAS will be scored on a scale of 0–10 which the higher the score, the more severe the sign. The record will be made once a day and 7 days a week. The investigators will use the average VAS scores as the symptom intensity score for the week. The change in each symptom’s score at 8 weeks after randomization relative to the baseline will be evaluated.

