### Sample size calculation

The study’s treatment duration will be 8 weeks, with the responder rate of the clinical symptoms of FD-PDS after 8 weeks of treatment being the primary efficacy endpoint. To control the overall false-positive error in the trial and to ensure the power of the test, the study will adopt the following assumptions: alpha level of 0.05 (2-sided) and power of 0.8, with the ratio of the number of cases in the ZZKZ group and the placebo group as 1:1. According to the results of a multicenter clinical study of ZZKZ completed by [name] in the First Affiliated Hospital of Sun Yat-sen University, with the cooperation of 16 domestic hospitals, the responder rate for clinical symptoms of FD-PDS has been set 54% with the ZZKZ and 38% for the placebo [16]. Calculation of sample size indicates that 187 cases will be required in the ZZKZ and placebo groups respectively. Assuming a dropout rate of 20%, a total of 480 cases will be required for our study.

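### The 0.05 significance rule covers every secondary test with no order or adjustment; the overall error statement is true only for the primary endpoint

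*Protocol article*

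**What the plan says.** The Statistical analysis section of the protocol article states: "All statistical tests will use a two-sided test, *P* ≤ 0.05 will be regarded as significant". The section puts the secondary outcomes in no order, makes none conditional on the primary result, adjusts no P value, and does not call the secondary analyses exploratory.

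The Sample size calculation section opens its list of assumptions with "To control the overall false-positive error in the trial and to ensure the power of the test, the study will adopt the following assumptions". The assumptions that follow are "alpha level of 0.05 (2-sided) and power of 0.8", for one endpoint, the responder rate at 8 weeks.

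Under Secondary outcomes the article lists:
- eleven symptom scores on the visual analogue scale, in a list that begins "including abdominal distension (mid-epigastric distension or lower abdominal distension), abdominal pain (mid-epigastric pain or lower abdominal pain), epigastric burning sensation, nausea", each assessed as change from baseline at week 8;
- the overall response on the 7-point scale at week 8;
- the SFNDI, which has five subscales, at weeks 4 and 8;
- the HAD anxiety and depression totals at weeks 4 and 8.

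The Statistical analysis section adds repeated-measures analysis of the symptom scores over time, sub-analyses by demographic data across countries, and Fisher tests on adverse events.

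**The concern.** The rule is stated, so this is more than a silence that an analysis plan could fill. It lets any secondary result at or below 0.05 be called significant, whether or not the primary endpoint succeeds. With this many comparisons, some will probably cross 0.05 by chance in a substantial share of trials of an inactive product. A single symptom, quality-of-life or mood score could then be reported as a significant effect.

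The mood scores are a case in point. The Background names improvement in anxiety and depression among the questions on which long-term evidence is lacking, and the Discussion gives this as the reason for using the HAD.

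The phrase about the overall false-positive error in the trial could also lead a reader to believe that secondary findings are protected at 0.05. Under the stated rule they are not.

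**Working it through.** **The plan's own figures.** The article gives neither a number of secondary comparisons nor an error rate across them, so there is no figure of that kind to reproduce. Its 0.05 relates to the sample size. With the stated inputs ("has been set 54% with the ZZKZ and 38% for the placebo", two-sided 0.05, power 0.8, 1:1) the usual formula for two proportions gives 152 per group, or 164 with continuity correction. The article states 187, which is not reproduced. At 187 per group the power is about 88%, so the primary comparison is not short of patients. A two-sided alpha of 0.025 would give 184, close to 187, but the article states no such alpha. The 187 therefore cannot be read as a hidden allowance for multiplicity.

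**Count of secondary comparisons** (a reader's count from the Secondary outcomes section).
- Symptom scores at week 8: 11
- Overall response at week 8: 1
- SFNDI at two visits: 2 as one score, or 5 × 2 = 10 as subscales
- HAD, two scores at two visits: 2 × 2 = 4

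Total: 11 + 1 + 2 + 4 = 18, or 11 + 1 + 10 + 4 = 26. Sub-analyses, other time points and adverse-event tests are left out.

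**Independent tests, no effect on any outcome.**
- At least one P ≤ 0.05 in either direction, 1 − 0.95^m: 1 − 0.95^18 = 0.603; 1 − 0.95^26 = 0.736.
- At least one false result favouring the product, 1 − 0.975^m: 1 − 0.975^18 = 0.366; 1 − 0.975^26 = 0.482.
- Expected number of false positives in either direction: 18 × 0.05 = 0.9; 26 × 0.05 = 1.3.

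**Correlated tests.** These scores come from the same patients, so independence is an upper benchmark. The documents give no correlations; a common correlation r between the test statistics is an assumption. With c = 1.96 and U standard normal, the chance in either direction is

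1 − E{[Φ((c − √r·U)/√(1 − r)) − Φ((−c − √r·U)/√(1 − r))]^m}.

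For results favouring the product only, the second Φ term is dropped.

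| Assumed correlation | Either direction, 18 tests | Either direction, 26 tests | Favouring product, 18 tests | Favouring product, 26 tests |
|---|---|---|---|---|
| 0 | 60% | 74% | 37% | 48% |
| 0.3 | 51% | 62% | 26% | 32% |
| 0.5 | 40% | 48% | 20% | 24% |
| 0.7 | 28% | 32% | 14% | 16% |

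One two-sided test has 5% in either direction and 2.5% in favour of the product. The smallest entries, 28% and 14%, are each more than five times those values.

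**The primary test.** There is one primary endpoint, tested at two-sided 0.05. Its error rate stays at 0.05 however many secondary tests follow, provided one of the two planned versions of the Cochran-Mantel-Haenszel test (with or without centre) is designated as primary.

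**The case against.** Four objections deserve an answer.

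1. *The error-control sentence concerns the primary endpoint only.* This stands. The sentence sits in the sample size paragraph, introduces the alpha and power for the 8-week responder rate, and holds for that endpoint. A reader might infer that the plan contradicts itself by promising control over all outcomes and then not delivering it. The article makes no such promise. What remains is wording wider than its content.

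2. *Multiplicity for secondary outcomes is usually left to the analysis plan, which is not shown.* This stands for a document that is silent. Here the article fixes a rule for all tests, and an analysis plan with a hierarchy or adjustment would depart from it.

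3. *The count of 18 to 26 is not in the article.* Correct. Only the overall response is expressly to be compared between groups; changes in the other scores are to be evaluated or calculated. No method is named specifically for the SFNDI or the HAD, and 26 requires separate tests of the subscales. The count shows what the rule reaches if each listed outcome is tested.

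4. *A false benefit is not likely.* This also stands. A reader might infer from 60% or 74% that an inactive product would probably show a significant benefit. Those figures include results favouring placebo and assume independence. For false benefits alone, no figure in the table exceeds 48%. Nor does the article claim in advance an effect on mood; it gives a reason to measure it.

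**Conclusion.** The point holds as a fault in the decision rule for secondary outcomes. It does not threaten the primary conclusion. Applied as written to the listed outcomes with no true effect, the rule gives a 28% to 74% chance of at least one significant secondary result in either direction, and a 14% to 48% chance of one favouring the product. The ranges span 18 to 26 comparisons and assumed common correlations from 0 to 0.7; the additional analyses are not counted. The statement on overall false-positive error is correct if confined to the primary endpoint and should be worded that way.

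**What to change.** In the Statistical analysis section, limit the claim of significance at two-sided 0.05 to the primary endpoint. In the Sample size calculation section, tie the error-control statement to that endpoint. Report secondary outcomes and sub-analyses as estimates with 95% confidence intervals and nominal P values that are not called significant.

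If the sponsor wants to make secondary claims, for example on HAD anxiety and depression, there are two options: a short sequence of the sponsor's choosing, fixed before unblinding and tested only after the primary succeeds, or a Holm adjustment. The documents do not dictate a particular order.

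The cost is one paragraph, and fewer secondary results can be called significant. The primary analysis and the sample size do not change.

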#### Withdrawal and dropout criteria

Investigators and subjects both can initiate withdrawal, while investigator-initiated withdrawals include (1) if the subject’s condition continues to worsen during the trial, and continuation of enrollment may lead to a serious adverse event; (2) during the trial, the subject experienced certain comorbidities, complications, or special physiological changes; (3) in the trial, subjects’ poor compliance, automatic change of medication, or concomitant use of prohibited medicinal products as specified in the protocol affected the determination of efficacy and safety; (4) adverse events or serious adverse events occur, and the investigators determine it is inappropriate for the subject to continue to receive the test treatment; (5) during the trial, cases were unblinded for various reasons; and subject withdrawals at discretion include (1) the subject perceives the efficacy as poor; (2) intolerance to certain adverse reactions; and (3) whatever the cause, the subject is unwilling to continue to participate in the clinical trial.

All subjects who complete the informed consent form and are deemed eligible to enter the randomized trial through screening, regardless of the reason for withdrawal, will be considered dropout cases as long as they do not complete the observation cycle specified in the protocol. This will include both the subject’s voluntary withdrawal and investigator-initiated withdrawal.

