### Outcomes

#### Primary outcome

Participants self-rate on the VAS for the degree of discomfort with both symptoms of postprandial fullness and early satiation, degree of discomfort will be indicated by a 10-cm line marked from 0 (asymptomatic or no discomfort) to 10 (extreme severe or extreme discomfort) [19]. The rating will be made once a day and 7 days a week via a diary card. For VAS scores for postprandial fullness discomfort and early satiety, the integral average for both symptoms over the past week will be evaluated, and a 50% decrease from baseline in the integral average at 8 weeks will be recorded as a response. The proportion of the response at 8 weeks after randomization will be considered the primary efficacy endpoint.

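### Last observation carried forward is the stated rule for missing week-8 response; intention-to-treat does not justify it, and it can bias the primary comparison by an amount the document cannot fix

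*Protocol article*

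**What the plan says.** The primary outcome is binary. The weekly average of the two symptom scores is compared with baseline, and "a 50% decrease from baseline in the integral average at 8 weeks will be recorded as a response". The endpoint is tied to one time point: "The proportion of the response at 8 weeks after randomization will be considered the primary efficacy endpoint" (Primary outcome).

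The Statistical analysis section gives the missing-data rule, "Based on the intention-to-treat principle, the missing data will be replaced by the last data", and explains it in brackets: "the missing efficacy data will be replaced by the efficacy data of the previous follow-up". On the population it says: "The efficacy analysis will be mainly based on a full analysis set".

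Under Withdrawal and dropout criteria, eligible patients, "regardless of the reason for withdrawal, will be considered dropout cases as long as they do not complete the observation cycle specified in the protocol". The reasons a patient may give for leaving include "the subject perceives the efficacy as poor; (2) intolerance to certain adverse reactions". Investigator-initiated reasons include worsening, adverse events, poor compliance and prohibited medication.

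Sample size calculation assumes 54% v 38% response, 20% dropout and 480 patients in total.

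**The concern.** Carrying the last value forward assumes that a patient's status at the last visit still holds at week 8. The Background and Discussion sections describe the condition as one that tends to come back, so this assumption is not a safe one here.

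The listed reasons for leaving are related to outcome or treatment. Patients who leave because the drug does not help will usually carry forward non-response. Patients who leave because of "intolerance to certain adverse reactions" may carry forward a response. If the mix of reasons differs between ZZKZ and placebo, the rule scores the same absence at week 8 differently by arm. The superiority test then partly reflects when and why patients left.

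The appeal to intention-to-treat does not help. That principle keeps every randomised patient in the assigned arm; what value to give an unobserved outcome is a separate assumption needing its own justification.

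For the continuous VAS outcomes, which the plan analyses by repeated-measures analysis of variance, carried-forward values would be treated as if observed, and the variability misstated.

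**Working it through.** **Inputs from the protocol article.** Planned response 54% v 38%, a difference of 16 points; two-sided alpha 0.05; 480 patients at 1:1, so 240 per arm; dropout 20% (all from Sample size calculation and Statistical analysis).

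**The plan's own figure.** 187 / (1 − 0.20) = 233.75, so 234 per arm and 468 in total; 480 covers this. The 187 itself does not follow from the stated inputs (the usual pooled formula gives 152), but that is a separate matter and nothing below depends on it.

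**Exposure.** 0.20 × 240 = 48 patients per arm, 96 in all, could have a carried-forward week-8 status.

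**Shift in the estimate.** Let d be the dropout share (equal in both arms) and q1, q0 the shares of ZZKZ and placebo leavers who carry forward a response. If leavers are in truth not week-8 responders, the shift in the estimated difference is d × (q1 − q0). At d = 0.20, a 10-point gap gives 0.20 × 10 = 2 points.

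**False-positive rate when there is no true difference.** Assumptions, not in the document: 38% of completers respond in both arms, and leavers are not week-8 responders. The observed rate per arm is (1 − d) × 0.38 + d × q. Rejection uses the pooled two-proportion z-test with 240 per arm (normal approximation).

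| d | q1 v q0 | Rates after carrying forward | Shift (points) | False positives |
|---|---|---|---|---|
| 20% | 40% v 40% | 38.4% v 38.4% | 0 | 5% |
| 20% | 40% v 20% | 38.4% v 34.4% | +4 | 15% |
| 20% | 40% v 10% | 38.4% v 32.4% | +6 | 28% |
| 10% | 40% v 20% | 38.2% v 36.2% | +2 | 7% |
| 10% | 40% v 10% | 38.2% v 35.2% | +3 | about 11% |

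Example, third row: 0.8 × 0.38 + 0.2 × 0.40 = 0.384 and 0.8 × 0.38 + 0.2 × 0.10 = 0.324. Simulating 200,000 trials gave 27.8% for this row and 10.6% for the last.

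**Opposite direction.** With completers at the planned 54% and 38%, d = 20% and q1 v q0 = 20% v 40%, the rates are 0.8 × 0.54 + 0.2 × 0.20 = 47.2% and 0.8 × 0.38 + 0.2 × 0.40 = 38.4%. The difference is 8.8 points and power about 50%.

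**Power if leavers count as non-responders** (completers at 54% and 38%, 240 per arm):

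- 20% dropout in both arms: 0.8 × 0.54 = 43.2% v 0.8 × 0.38 = 30.4%; difference 12.8 points, power 83%.
- 25% v 15%: 0.75 × 0.54 = 40.5% v 0.85 × 0.38 = 32.3%; difference 8.2 points, power 46%.

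**The case against.** The strongest reply is that the 28% is partly built in. The calculation takes leavers to be non-responders, which is also the rule that non-responder imputation applies, so that rule must score 5%. The article does not say that stopping means non-response. The 40% v 10% split is assumed as well. This stands: the figure is one end of a range, and the range includes no bias at all. A reader might infer that the plan has a 28% false-positive rate; the document gives no dropout by arm, timing or reason, so it does not support that.

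Second, 20% may overstate the missing week-8 data. Dropout means not completing the observation cycle, and the Abstract gives 8 weeks of treatment plus 4 weeks of follow-up. If the cycle includes follow-up, patients lost in weeks 9 to 12 count as dropouts but already have the primary endpoint. This also stands, and it is why the 10% rows are shown. The visit schedule is in a figure not shown, so how old a carried value could be is unknown.

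Third, a reader might infer that no other missing-data method or sensitivity analysis is planned. The article is condensed and the SAP is not at hand, so that cannot be concluded. The point rests on the rule the article does state; a sensitivity analysis elsewhere would leave that rule in place.

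Fourth, the intention-to-treat sentence can be read as meaning only that values are filled in so that patients stay in the full analysis set. That softens the criticism of the wording, but carrying forward remains the rule for filling them in.

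Finally, non-responder imputation is also single imputation and is sensitive to unequal dropout. With 38% of completers responding in both arms and 25% v 15% dropout it gives 28.5% v 32.3%, a difference of −3.8 points. This stands and shapes the fix.

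**Conclusion.** The concern holds as a conditional weakness in a stated rule that governs the primary test. An early leaver with a sufficient fall in score is counted as responding at week 8, and the reason given for this does not support it.

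At 20% dropout, gaps of 0 to 30 points in carried-forward response shift the estimate by 0 to 6 points, against a planned effect of 16, with false-positive rates of about 5% to 28%. At 10% dropout, gaps of 20 and 30 points give about 7% and 11%. These rates assume equal dropout in the two arms, 38% response among completers of both arms, and leavers who are in truth not week-8 responders. A gap in the other direction would hide a real effect. Neither direction nor size can be determined from the document.

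**What to change.** Amend the protocol, and the SAP to match, before unblinding:

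- For the primary endpoint, replace carrying forward with non-responder imputation when no evaluable week-8 diary score exists.
- State, as part of the estimand, whether stopping study drug before week 8 also counts as non-response when a week-8 score is available.
- Support this with multiple imputation by arm under missing-at-random and a tipping-point analysis. Keep carrying forward at most as a sensitivity analysis.
- Analyse the continuous VAS outcomes with a likelihood-based repeated-measures model on the observed data.
- Drop the appeal to intention-to-treat as the reason for the imputation rule.

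**Cost.** Changes to wording and analysis programs; no extra patients or visits. The article describes a route for amendments, and treatment codes are withheld until the analysis, so the change can be made blind. Reported response rates will fall. Power stays above the planned 80% if dropout is 20% in both arms (83%), but falls to about 46% at 25% v 15%. The multiple-imputation and tipping-point analyses are therefore needed alongside the primary rule, to show how far the result depends on it.

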### Eligibility criteria

#### Inclusion criteria

(1) Outpatients aged 18–65 years; (2) meeting the Rome IV diagnostic criteria for FD-PDS; (3) able to discontinue prohibited medications that may affect the evaluation of the effectiveness; (4) with Visual Analogue Score (VAS) score ≥ 4 for major symptoms (at least one of postprandial fullness discomfort and early satiety); and (5) informed and voluntarily sign the informed consent form.

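### The primary responder comparison leaves out the baseline composite VAS that the endpoint already requires; adjusting for it might narrow the confidence interval, by an amount that could be nil

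*Protocol article*

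**What the plan says.** The Statistical analysis section of the protocol article compares efficacy between groups by a Cochran-Mantel-Haenszel chi-square "test with and without regard to center stratification, and a 95% confidence interval of the difference between groups will be calculated". It names the full analysis set as the main set and says that a centre effect will be considered. No baseline covariate is named for this comparison.

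Under Primary outcome, the two symptom scores (postprandial fullness and early satiation) are averaged over the past week, and "a 50% decrease from baseline in the integral average at 8 weeks will be recorded as a response". The baseline composite is therefore part of the endpoint.

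Randomization is stratified by hospital only. Entry requires patients "with Visual Analogue Score (VAS) score ≥ 4 for major symptoms", on at least one of the two symptoms, so the composite of both can vary considerably between patients at entry.

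The Sample size calculation uses "alpha level of 0.05 (2-sided) and power of 0.8". The responder rate "has been set 54% with the ZZKZ and 38% for the placebo", and 480 patients are planned in total.

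**The concern.** A baseline measurement of the outcome is usually the first candidate for covariate adjustment. Here it has to exist for the endpoint to be computed, so using it needs no extra visit, instrument or patient. Neither the randomization nor the primary test takes it into account.

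If baseline severity predicts who halves their score, an adjusted comparison gives a narrower interval for the same risk difference and removes the part of the estimate that comes from chance baseline imbalance. What is at stake is the width of the primary confidence interval and some power. The type I error rate and the meaning of the endpoint are not affected.

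**Working it through.** **1. The plan's own figures.** With 54% versus 38%, two-sided alpha 0.05 and power 0.80, the usual two-proportion formula gives 152 per arm (pooled variance), 164 (continuity-corrected) or 149 (unpooled). None of these is the stated 187. The unpooled figure divided by 0.8 is 149/0.8 = 186.25, which rounds up to 187, so dropout may already be in that number. That is a separate matter to reconcile. For the present point, the planned size is more than the stated inputs need: unadjusted power is 87.7% at 187 per arm and 94.3% at 240 per arm.

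**2. When baseline predicts response.** Let B be the baseline composite and W the week-8 composite. Response means W ≤ 0.5B, or D = W − 0.5B ≤ 0. With SDs s_B and s_W and correlation ρ:

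corr(D, B) = (ρ·s_W − 0.5·s_B) / √(s_W² − ρ·s_W·s_B + 0.25·s_B²)

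This is zero when ρ = 0.5·s_B/s_W, that is, when week-8 scores rise by 0.5 cm per 1 cm of baseline. Below that value, patients with a high baseline respond more often; above it, less often.

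**3. Variance of response explained.** For a binary response with proportion p and roughly normal scores, R² ≈ corr(D, B)² · φ(z_p)² / [p(1 − p)]. I take p = 0.46, the midpoint of 54% and 38%. Then φ(z_p) = 0.397 and the multiplier is 0.1576/0.2484 = 0.634.

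The SDs are not in the documents. Assumed pairs (s_B / s_W) are 1.3/2.2 and 1.8/2.4, with an assumed baseline mean of 5.5. The zero points are 0.5 × 1.3/2.2 = 0.30 and 0.5 × 1.8/2.4 = 0.375.

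Worked example at ρ = 0 and 1.3/2.2: corr = −0.65/√(4.84 + 0.4225) = −0.283, and R² = 0.634 × 0.0803 = 0.051.

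| ρ | R², SDs 1.3/2.2 | R², SDs 1.8/2.4 |
|---|---|---|
| 0 | 0.051 | 0.078 |
| 0.3 | 0.000 | 0.004 |
| 0.4 | 0.008 | 0.001 |
| 0.5 | 0.034 | 0.013 |
| 0.6 | 0.080 | 0.047 |
| 0.7 | 0.154 | 0.109 |

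Simulation under the same assumptions gives the same picture: 0.05-0.08 at ρ = 0, 0.00-0.003 at 0.3, 0.01-0.03 at 0.5, 0.05-0.08 at 0.6 and 0.11-0.15 at 0.7. The SDs matter. With 1.0/2.0, simulated R² at ρ = 0.6 is about 0.10.

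**4. In patients.** The saving is about R² × N. At 8% it is 0.08 × 480 = 38, so the range for ρ from 0 to 0.6 is about 0-40 patients. At ρ = 0.7 it is 0.11 × 480 = 53 to 0.15 × 480 = 72.

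**5. In interval width.** Unadjusted, with 240 per arm, the half-width is 1.96 × √[(0.54 × 0.46 + 0.38 × 0.62)/240] = 1.96 × 0.0449 = 8.8 percentage points. Multiplying by √(1 − R²) gives 8.6 at R² = 0.05, 8.4 at 0.08 and 8.1 at 0.15.

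**6. In power.** At 240 per arm, power rises from 94.3% to 95.3% at R² = 0.05 and 96.2% at 0.10. At 187 per arm it rises from 87.7% to 89.3% and 90.8%.

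**7. Does adjustment cost precision?** In simulated trials of 480 patients in 18 hospitals at 54% versus 38%, a linear risk-difference model with hospital and baseline was compared with one using hospital only. The ratio of standard errors was 0.97 at ρ = 0, 1.00 at 0.35, 0.99 at 0.5, 0.97 at 0.6 and 0.94 at 0.7. The mean estimated difference stayed at about 0.16. The worst case was no gain.

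**The case against.** A hospital-stratified CMH test with a 95% CI of the difference is a standard analysis that respects the randomization. Nothing in it is wrong, and randomization already protects validity against baseline imbalance. That stands. A reader might infer that leaving baseline out biases the comparison or inflates the type I error; the documents do not support that.

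A reader might also infer that the plan certainly gives up precision. That does not hold either. Baseline already enters through the halving rule, so its remaining association with response can vanish or take either sign, and the documents contain nothing from which to size it. Even at R² = 0.05 the half-width only moves from 8.8 to 8.6 points, and power is already above the 80% target.

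Nor is the change free. Recruitment began in October 2019, and the section on protocol amendments requires agreement of the principal investigator and sponsor, ethics resubmission, a registry update and approval at the other centres. A logistic model with 18 hospital terms, averaging 480/18 ≈ 27 patients each, can also fail in a hospital where all or no patients respond. CMH handles such strata without difficulty. This stands, and the fix has to provide for it.

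The remaining argument is that an analysis plan, not shown here, may add an adjusted analysis. It may. But the article names the primary test, and the point concerns that named test.

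**Conclusion.** The point holds as a modest one about efficiency. The stated primary comparison does not use a baseline value that the endpoint already requires, and using it could narrow the interval for the same risk difference. Under the assumed SDs the gain is worth about 0-40 of 480 patients for baseline-to-week-8 correlations of 0 to 0.6 and about 53-72 at 0.7. It is near zero at 0.3-0.4. No meaningful loss of precision is expected at this sample size.

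Apart from the responder rates and the planned 480, every input to these figures is an assumption, and the gain may be nil. The planned analysis remains valid.

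**What to change.** Before level I of the blind code is opened, pre-specify as the primary analysis a risk difference in week-8 response with its 95% CI, adjusted for hospital and for baseline composite VAS as a continuous covariate. Use a method that tolerates hospitals in which all or no patients respond. Examples are a linear risk-difference model with robust standard errors, or a logistic model standardised to a marginal risk difference with small hospitals pooled by a rule fixed in advance. Keep the hospital-stratified CMH test as a supportive analysis.

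The endpoint, the data collected and the interpretation of the difference stay the same. The costs are that a model replaces a simple table test, that a protocol amendment has to go through the process the article describes, and that the effort may bring no gain. Added after unblinding, the adjustment would be post hoc.

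### The secondary VAS endpoint is change from baseline at week 8, but the stated analysis is a repeated-measures ANOVA across time points on LOCF-filled data, with no week-8 contrast named

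*Protocol article*

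**What the plan says.** Protocol article, VAS score of each FD symptom: eleven symptoms are scored daily from 0 to 10 and averaged by week: "The investigators will use the average VAS scores as the symptom intensity score for the week". The endpoint is one contrast in time, the change in each symptom's "score at 8 weeks after randomization relative to the baseline will be evaluated".

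Protocol article, Statistical analysis: "Method repetitive measure analysis of variance will be used to analyze the secondary outcome of VAS scores at different time points between groups". For missing values, "the missing efficacy data will be replaced by the efficacy data of the previous follow-up". On the analysis set: "The efficacy analysis will be mainly based on a full analysis set".

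The section names no week-8 contrast. It does not say whether baseline is one of the time levels, a covariate or neither. The Blinding section refers to a statistical analysis plan, which is not shown.

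**The concern.** The endpoint and the analysis are both stated, and they do not meet. A repeated-measures ANOVA over several time points reports two things by default: a group effect averaged over all of them, and a global test of whether the group profiles differ. The first answers a different question from the week-8 change. The second gives no estimate. An analyst following the text could report either as the result for this endpoint.

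The missing-data rule adds to this. The article's own content makes informative dropout plausible:

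- Sample size calculation assumes 20% dropout.
- Withdrawal and dropout criteria lists worsening, perceived lack of efficacy and intolerance of adverse reactions as reasons to leave.
- The Discussion concedes that daily diary completion may be hard to sustain.

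If patients improve over the 8 weeks, carrying an early score forward freezes a dropout at a worse value than would have been reached. The size of that error depends on how many leave each arm, and when. The filled values then count as real measurements in the standard error.

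**Working it through.** The article gives no sample size, SD or correlation for the VAS change endpoint, so there is no stated figure to reproduce. Its sample size concerns the primary responder rate and does not bear on this point. Every number below except the 20% dropout rests on an assumption, named where it is used.

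**1. What the ANOVA estimates.** Let d(w) be the treatment difference at week w, with d(0) = 0 by randomisation.

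- Endpoint: d(8) - d(0) = d(8).
- Interaction contrast of week 8 against baseline, if baseline is a time level: also d(8).
- Group main effect: the average of d(w) over the time levels.

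Assume weekly levels and linear onset, d(w) = (w/8) × d(8):

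- Baseline included (weeks 0 to 8): mean of w/8 = 4/8 = 0.50 of d(8).
- Baseline excluded (weeks 1 to 8): 4.5/8 = 0.56 of d(8).

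This overstates the loss of power, because averaging also reduces variance. With equal correlation c between the eight weeks, the mean has variance (1 + 7c)/8 relative to one week. At c = 0.5 this is 0.5625, an SD of 0.75, so the standardised effect is 0.5625/0.75 = 75% of that at week 8. At c = 0.3 it is about 90%, and at c = 0.7 about 66%. An early plateau would dilute the effect little or not at all. What remains is that the wrong quantity is estimated, more than that power is lost.

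**2. What LOCF does to the week-8 change.** Assumed: placebo change -2, active change -2.6 (true difference -0.60), linear onset, last observed week uniform over 0 to 7, dropout unrelated to outcome within an arm. A dropout keeps on average 3.5/8 = 0.4375 of the full change. With dropout fraction p, the arm mean is the full change × (1 - 0.5625p).

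| Dropout active / placebo | Active | Placebo | Difference |
|---|---|---|---|
| 20% / 20% | -2.6 × 0.8875 = -2.31 | -2 × 0.8875 = -1.78 | -0.53 |
| 25% / 15% | -2.6 × 0.8594 = -2.23 | -2 × 0.9156 = -1.83 | -0.40 |
| 15% / 25% | -2.6 × 0.9156 = -2.38 | -2 × 0.8594 = -1.72 | -0.66 |

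With no true effect (both arms -2) and 25% / 15% dropout, the difference is -2 × 0.8594 + 2 × 0.9156 = +0.11. The reverse split gives -0.11. A simulation of 1,500 trials per scenario (240 per arm, SD 2, correlation 0.5 between all weeks) agreed: -0.53, -0.40 and -0.67, and a spurious 0.11 to 0.12 in either direction under no effect. Outcome-related dropout was not simulated.

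**3. What baseline adjustment is worth.** Let r be the baseline-to-week-8 correlation, with equal variance at both times. Relative variances are 1 for the unadjusted week-8 score, 2(1 - r) for unadjusted change and 1 - r² for the baseline-adjusted contrast.

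| Assumed r | Adjusted | Change | Ratio to change, (1 + r)/2 | Ratio to week-8 score, 1 - r² |
|---|---|---|---|---|
| 0.3 | 0.91 | 1.40 | 0.65 | 0.91 |
| 0.5 | 0.75 | 1.00 | 0.75 | 0.75 |
| 0.7 | 0.51 | 0.60 | 0.85 | 0.51 |

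**The case against.** The strongest reply is that one condensed sentence is being asked to carry too much. Four parts of it stand.

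- A reader might infer that the named ANOVA cannot estimate the endpoint. It can: with baseline as a time level, the week-8-versus-baseline interaction contrast is exactly the difference in change. The gap is that the contrast is not named.
- A reader might infer that raw scores will be analysed without baseline adjustment. The article says neither. Covariates and covariance structure are commonly left to the analysis plan, which is not shown, and so is any handling of sphericity. Under randomisation, omitting baseline costs precision, not validity.
- A reader might take the 0.50 or 0.56 fraction as the loss. It depends on linear onset, which the documents do not give, and it ignores the variance saved by averaging.
- LOCF bias is not certain. With equal, outcome-unrelated dropout it is a modest attenuation in the example. The rule is also a general one, not specific to this ANOVA.

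The reply does not dispose of the rest. Leaving detail to the analysis plan excuses silence, but the method and the imputation rule are both stated. Neither default output of that method is the stated endpoint, and the rule can shift the week-8 estimate in either direction.

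**Conclusion.** The point holds in limited form. The stated analysis does not name the contrast that the stated endpoint requires, and the fixed LOCF rule can distort that contrast while treating imputed values as observed. In the worked example a true -0.60 becomes anything from -0.40 to about -0.66, and a null effect becomes about 0.11 in either direction when dropout differs by 10 percentage points. These sizes rest on the assumed placebo change, onset and dropout timing, and other inputs would move them.

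The precision gain from baseline adjustment depends on r and on the comparator. For r from 0.3 to 0.7 the variance ratio runs from 0.65 to 0.85 against unadjusted change, and from 0.91 to 0.51 against the unadjusted week-8 score. The article does not say which unadjusted analysis would otherwise be used, so the gain is a reason to prefer the replacement and not a proven defect of the plan.

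Only secondary outcomes are concerned. The primary Cochran-Mantel-Haenszel comparison is touched only through the shared LOCF rule. The change is worth making before unblinding.

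**What to change.** Replace the repeated-measures ANOVA with a mixed model for repeated measures on the observed weekly mean of each symptom:

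- fixed effects for treatment, week, treatment-by-week, baseline score, baseline-by-week and centre;
- unstructured covariance across weeks;
- the week-8 treatment contrast, with its 95% CI, as the stated result. With baseline in the model this contrast is the same whether the response is the score or the change.

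Fit the model without LOCF, and keep LOCF at most as a sensitivity analysis. The model relies on data being missing at random, which the listed withdrawal reasons may strain, so also prespecify a sensitivity analysis that departs from that assumption. The same model could serve the SFNDI and HAD changes at weeks 4 and 8, for which the article names no method. That is a suggestion, not a fault found.

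The cost is a change of wording in the protocol and analysis plan, a standard SAS procedure and the added sensitivity analysis. No new data are needed.
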